**Mixed methods analysis, and implementation of findings at the end of the pilot phase**

Following separate qualitative and quantitative data analyses the results will be merged into two ‘joint displays’, which combine the findings in a tabulated form, will be used to assess the ways in which the qualitative and quantitative data sets agreed (confirmed), complemented (offered an expanded explanation) or contradicted each other (59).

The first joint display will address the feasibility and acceptability of the BEAM platform and the trial procedures (using data from the internal pilot stage). This will be used to inform adaptations to the intervention and trial procedures, ahead of progression to the full trial.

An implementation group will be set up to enable rapid application of the qualitative findings in the main trial. This group will comprise the chief investigator, co-investigators, PPI representatives and representatives from participating centres. A meeting via videoconferencing will take place at the end of the pilot phase to enable the qualitative researchers to feedback their findings to the group so that recommendations can be implemented into the main trial.

The second joint display will combine data from the final interviews (relating to participant perception and experience) with trial data to facilitate a deeper understanding of the effects (or lack of effect) of the BEAM platform (using) (60).

**7.8 Qualitative Sub-Study- Digital Inclusion**

A qualitative sub-study will be conducted to explore aspects of digital inclusion and digital health literacy in participants who have declined participation to the study, or who have not engaged with the digital platform. This will help to refine the platform and ensure that this is in line with service users, as well as addressing potential inequalities in access to a digital health platform.

It is understood from the literature that there are some sections of the population who are more likely to be excluded. This includes:

- Older people
- People in lower income groups
- People without a job
- People in social housing
- People with fewer educational qualifications
- People living in rural areas

Individual interviews will be conducted, with up to 20 participants. Data collection will cease at the point where data saturation is achieved. Purposive sampling will be used to ensure varied experiences and viewpoints are represented, for example, those at different stages of CKD, representative of different ethnic backgrounds, gender, age and study regions.

Appropriate topic guides will be developed in advance of the study. Questions will be discussed within the project team and trial steering group. Participant information sheets will be sent via post, email or provided face to face. Interviews will be conducted by the experienced qualitative team, and supported by an individual undertaking a funded digital inclusion fellowship. Interviews will be conducted over the telephone, online, or in person if able, at an appointment separate from other trial assessments or discussions. Informed consent will be taken digitally prior to the discussion, or if access to the internet is not possible consent forms will be sent via post with a stamped addressed envelope for the participant to return. Individuals participating in this digital inclusion sub-study will be offered £20 to re-imburse their time to meet with the qualitative interviewer.

A questionnaire to collect demographic information will be completed by each participant at the start of the individual semi-structured interview. This will provide further demographic information about the participants in order to further understand potential barriers to digital inclusion. This information will be used to guide the sampling and to help explore the data during analysis.

The recorded interviews will be professionally transcribed verbatim. Transcripts will not include any identifying information; individual’s names and personal details will not be included in the completed transcripts but will be recorded and stored separately. Similarly, any written notes taken during the interviews will not include any identifiable personal data. Sampling will be as per sampling framework in Section 7.7

**Analysis and implementation of findings**

Analysis will be completed according to the methods outlined by Braun and Clarke, as outlined in the main qualitative study in 7.7.

**7.9 Expected Duration of Trial**

18 months (6 weeks set-up, 9 months recruitment, 3 months follow-up after intervention, 6 months long-term follow-up, 3 months analysis and write-up for main study).

| The end of the trial will be defined as last patient assessed. |
| --- |

**8. Laboratory Tests**

Before starting the study, the principal investigator at each participating site will supply the Sponsor with a list of the normal ranges and units of measurements for the applicable parameters measured in the study. Any changes to these ranges and units must also be notified to the Sponsor.

All laboratory parameters performed and assessed in local laboratories at each site will be reviewed at each visit assessment.

**Laboratory Parameters:**

*Biochemistry*

- Creatinine, eGFR, C-reactive Protein (CRP), Hemoglobin (Hb), IL-6, Albumin

### 9. Assessment of Safety

### 9.1 Specification, Timing and Recording of Safety Parameters.

### Serious adverse events will be identified and reported to the sponsor. In addition, episodes of hospitalisation and other infection episodes will be documented.

###

### 10. Statistics

### 10.1 Sample Size

The choice of endpoint measures to be studied have been chosen to provide clinical relevance. Studies that have evaluated the clinically meaningful change in MCS of the KDQOL-36 HRQoL questionnaire in people living with kidney disease (refs) indicate that a clinically meaningful improvement in MCS is 3AUs. An estimated sample size of 106 participants in each group (total N = 212) based on an MCS with a mean of 45, SD 10 and correlation between repeated measures of 0.7, would allow a clinically meaningful difference of 3AUs to be detected at 80% power and 5% alpha. We will recruit 304 participants in total to allow for potential dropouts of 30%.

**10.2 Randomisation**

Participants will be randomised using an approach based on randomly varying block sizes. The randomisation will be stratified by a single binary variable, defined by whether or not patients have diabetes, or not.

**10.3 Analysis**

Baseline demographics of the patients will be described using summary statistics. Continuous variables will be summarised using the mean and SD if approximately normally distributed. Continuous variables that are not normally distributed will be summarised using the median and interquartile range. Categorical variables will be summarised using frequencies and percentages. Comparisons will be made between the demographic variables of the control and intervention groups using t-tests, median tests and chi-square tests as appropriate.

Repeated measures analysis of variance will be employed to investigate the change from baseline to 12 weeks follow-up between the control and intervention groups for the primary outcome variable (MCS) and other parametric outcome measures. If the assumptions for parametric testing are not met, the equivalent non-parametric equivalent tests will be performed.

As this is the first study of this novel intervention, exploratory data analysis will also be undertaken to investigate possible associations between outcomes in order to frame future research questions.

Adverse events will be collected and analysed descriptively.

Statistical significance will be set at 5% and tests will be two-sided. The analysis will be undertaken in SPSS version 26.

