**4.1.1 Primary outcome measure**

Mental HRQoL as measured by MCS of the KDQOL-36 at 12 weeks.

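### The primary analysis named in 10.3 can use only participants with both MCS values, while 10.1 allows for 30% dropout; if loss differs by arm the estimate can be biased in either direction

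*Protocol*

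**What the plan says.** The primary outcome is defined in Protocol 4.1.1 as "Mental HRQoL as measured by MCS of the KDQOL-36 at 12 weeks". Section 10.3 names the method: "Repeated measures analysis of variance will be employed to investigate the change from baseline to 12 weeks follow-up between the control and intervention groups". If parametric assumptions fail, a non-parametric equivalent replaces it. The software is SPSS 26, and "Statistical significance will be set at 5% and tests will be two-sided".

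Section 10.1 arrives at 212 participants, 106 per arm. The inputs appear there as "based on an MCS with a mean of 45, SD 10 and correlation between repeated measures of 0.7". The target is a 3-unit difference in MCS with 80% power at the 5% level. Recruitment is then raised to cover losses: "We will recruit 304 participants in total to allow for potential dropouts of 30" per cent.

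Other sections bear on how many week-12 scores will be missing:

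- Section 6.5 does not replace withdrawn participants. Those who withdraw from the study are still to attend assessments. Those who withdraw consent contribute nothing further.
- The pilot progression criteria in 4.2 rate KDQOL completion of at least 80% as Go and at least 70% as Amber. For dropout, under 20% is Go and under 40% is Amber.
- The same criteria record post-randomisation withdrawals by group, to judge whether the waitlist design is acceptable.
- Section 5.1 blinds the outcome assessor only.

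**The concern.** In a two-time-point repeated-measures ANOVA, the group-by-time test is a comparison of mean change between arms. A participant with no week-12 score has no change score and does not enter. The non-parametric fallback has the same limit if it also tests change. The protocol does not mention deleting incomplete cases; that follows from the method it names.

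The analysis is therefore of those who supplied both scores. This is harmless if loss has nothing to do with baseline score or outcome. It is not harmless if loss differs by arm in a way linked to either, and here that is plausible: one arm is encouraged to attend two sessions a week (7.4), the other waits, and both know which they are in. Section 4.1 says the results are meant to support commissioning, where the relevant effect is the one in everyone offered the platform.

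**Working it through.** **1. Reproduce the plan's sample size.** Inputs from 10.1: difference 3, SD 10, correlation 0.7, power 80%, alpha 5%; two-sided from 10.3.

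- SD of change = 10 × √(2 × (1 − 0.7)) = 7.746.
- Normal approximation: 105 per group. With the noncentral t, 106 per group gives power 0.801. The plan's 106 is reproduced.
- Other variances do not match. The baseline-adjusted SD, 10 × √(1 − 0.49) = 7.141, needs 89 per group; the unadjusted SD of 10 needs 175.
- 212 / 0.70 = 302.9, so 303, or 304 at 152 per group.

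The arithmetic is right, and it shows that the trial is sized on change scores in completers. 304 × 0.30 = 91.2, so about 91 participants could be absent from the primary estimate.

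**2. Loss related to baseline MCS in one arm.** Assumption: 30% loss in each arm, random in control; in the intervention arm the log-odds of loss change by 1 per SD of baseline MCS. True effect 3, one million simulated participants per arm, SD and correlation from 10.1.

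| Who leaves the intervention arm | Change-score estimate | Baseline-adjusted |
| --- | --- | --- |
| Low baseline MCS | 2.25 | 3.01 |
| High baseline MCS | 3.76 | 3.01 |

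The size can be checked by hand. With correlation 0.7, expected change falls by 0.3 for each point of higher baseline. A bias of 0.75 corresponds to stayers' mean baseline being shifted by 0.75 / 0.3 = 2.5 points. A separate run gave 2.23 and 3.78, and multiple imputation from baseline returned 3.00.

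**3. Leavers who do not benefit.** Assumption: stayers gain 3 and leavers gain 0. Effect in all randomised = 3 × (1 − loss in the intervention arm).

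| Intervention-arm loss | Completers | All randomised | Gap |
| --- | --- | --- | --- |
| 20% | 3.0 | 3 × 0.8 = 2.4 | 0.6 |
| 30% | 3.0 | 3 × 0.7 = 2.1 | 0.9 |

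At 30% loss the standard error is √(2 × 60 / 106) = 1.06, where 60 is 7.746², so the gap is about 0.85 standard errors. Both figures for all randomised lie below the 3-unit threshold in 10.1.

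**4. Loss related to the change itself.** True effect 3, 30% loss per arm, log-odds slope of 0.5 to 1 per SD of change (assumed).

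- Poor responders leave the intervention arm only: 4.1 to 5.0.
- Poor responders leave control only: 1.9 to 1.05.
- Same mechanism and rate in both arms: about 3.0.
- Loss completely at random: 2.99.

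**5. What imputation can and cannot repair.** It corrects step 2. In step 3 at 30% loss, imputation from baseline gives 3.02 against a completers' 3.02, with 2.11 in all randomised, so nothing is gained. Jump to reference gives 2.11, but only because it builds in the same zero-gain assumption. In the first case of step 4, baseline adjustment still leaves 3.9 to 4.7.

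**The case against.** The strongest reply is that missing-data rules, analysis sets and sensitivity analyses usually sit in the statistical analysis plan, which is not at hand. That is fair, and their absence from the protocol is not the point made here. What stands is that 10.3 names a specific primary method that cannot use participants lost before week 12. An analysis plan that follows it inherits the limit, and one that departs from it contradicts the protocol.

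Second, 30% is an allowance and not a forecast. Section 6.5 keeps people who withdraw from the study in assessment, so someone who merely stops using the platform should still supply a week-12 score. The Go thresholds correspond to loss of 20% or less. This stands, and is why the 20% figure is shown beside the 30% one.

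Third, the 2.4 and 2.1 follow directly from assuming zero gain in leavers. That also stands: they show what would be at stake under that assumption and are not evidence about this trial.

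A reader might infer that the estimate will be overstated because only the intervention arm has a reason to lose non-responders. The documents do not support this. Waitlist participants can leave too, and 4.2 tracks withdrawals by group for that reason. Loss of poor responders from control alone would understate the effect.

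**Conclusion.** The concern holds in limited form. The named analysis uses only participants with both MCS values, and the plan's own arithmetic treats up to about 91 of 304 as lost to it. If loss differs by arm and relates to baseline score or outcome, the estimate is biased, in a direction the documents do not settle. Under the assumed mechanisms a true effect of 3 appears as about 2.2 or 3.8 when loss depends on baseline MCS in one arm. If leavers gain nothing, the completers' 3.0 stands against 2.4 or 2.1 in all randomised. There is no bias if loss is unrelated to baseline score and outcome, and essentially none if the same mechanism acts at the same rate in both arms. SD and correlation are the protocol's; the loss mechanisms and the zero gain are assumptions.

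It would go too far to say that the protocol expects 30% to be missing, or that it deliberately restricts the analysis to those who used the platform. It states neither.

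**What to change.** In 10.3, replace the repeated-measures ANOVA with an analysis of all randomised participants by allocation, using a baseline-adjusted model for week-12 MCS. Handle missing week-12 scores by multiple imputation from baseline MCS, arm, diabetes (the stratification factor) and the other baseline scores already collected, or use a likelihood-based model. State how deaths before week 12 are handled, and do not impute scores for them silently.

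Imputation under missing-at-random does not correct outcome-related loss. Add one prespecified missing-not-at-random sensitivity analysis, such as jump to reference for the intervention arm, where missing scores are drawn as if from the waitlist arm. Report it beside the primary result and not as a second condition for success.

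The cost is revised wording and a few hours of statistician time, with no new data. Baseline adjustment does not cost power: on the plan's inputs, 106 per group gives about 86% against about 80% for change scores. The downside is that the sensitivity estimate is likely to be smaller than the primary one.

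### A baseline-adjusted ANCOVA in place of the repeated-measures ANOVA of MCS change would raise power from about 80% to 86% at 106 per arm, at no cost to the trial

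*Protocol*

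**What the plan says.** Section 10.3 fixes the method for MCS and the other parametric outcomes: "Repeated measures analysis of variance will be employed to investigate the change from baseline to 12 weeks follow-up between the control and intervention groups". It names no covariate. It also states: "Statistical significance will be set at 5% and tests will be two-sided".

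Section 10.1 sizes the trial at 106 per group, "based on an MCS with a mean of 45, SD 10 and correlation between repeated measures of 0.7", which "would allow a clinically meaningful difference of 3AUs to be detected at 80% power and 5% alpha". The total of 304 allows for 30% dropout.

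Section 10.2 says of allocation: "The randomisation will be stratified by a single binary variable, defined by whether or not patients have diabetes, or not". Section 10.3 does not mention diabetes.

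Section 4.1.1 sets the primary outcome as MCS at 12 weeks, so the primary comparison uses two measurements per participant, baseline and week 12.

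**The concern.** With two time points, the group-by-time test of a repeated-measures ANOVA is the same as a two-sample t-test on change from baseline. That test subtracts the whole baseline value, which fixes the baseline slope at 1. If the SD is the same at both visits, the protocol's correlation of 0.7 implies a slope of 0.7. ANCOVA estimates the slope from the data, and its large-sample variance cannot exceed that of the change score.

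What is at stake is precision on the primary outcome. The interval for the MCS difference would be wider, and the chance of detecting a 3-point effect lower, than the same participants could give. The loss is larger if the true correlation is below 0.7, and section 10.1 gives no source for that value.

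**Working it through.** **Inputs.** From section 10.1: difference 3 AU, SD 10, correlation r = 0.7, 106 per group, 80% power, 30% dropout, 304 in total. From section 10.3: two-sided 5%. From section 6.4: 1:1 allocation. Assumption: the SD is 10 at both visits. The protocol gives only one SD.

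**Step 1: reproduce the plan's figure.** The SD of change is SD × √(2(1 − r)) = 10 × √0.6 = 7.746.
- Normal approximation: n per arm = 2 × 60 × (1.960 + 0.842)² / 3² = 104.7, so 105. The noncentral t version gives exactly 106.
- Dropout: 212 / 0.70 = 302.9, so 303. The stated 304 (152 per arm) is the next even number.
- Other candidates do not give 106. The week-12 score alone (SD 10) needs 175 per arm by the normal approximation. ANCOVA needs 89, or 90 with t. A one-sided change-score test needs 83.

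The sample size was therefore built for the change-score test, and sections 10.1 and 10.3 agree.

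**Step 2: same inputs, ANCOVA.** The residual SD is SD × √(1 − r²) = 10 × √0.51 = 7.141. The variance ratio to the change score is (1 − r²) / (2(1 − r)) = 0.51 / 0.60 = 0.85, which is 15% lower.

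**Step 3: precision and power at 106 per arm.** The standard error is the SD × √(2/106), and the t critical value on 210 df is 1.971.
- Change score: SE = 7.746 × 0.1374 = 1.064; half-width 1.971 × 1.064 = 2.10 AU; noncentrality 3 / 1.064 = 2.82; power 80.1%.
- ANCOVA: SE = 7.141 × 0.1374 = 0.981; half-width 1.971 × 0.981 = 1.93 AU; noncentrality 3 / 0.981 = 3.06; power 86.1%.

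The one or two degrees of freedom that the covariates use are ignored. With more than 200 available, the effect is negligible.

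**Step 4: sensitivity** (noncentral t, difference 3, SD 10).

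| r | n per arm | Change score | ANCOVA | Gain (points) |
|---|---|---|---|---|
| 0.6 | 106 | 68.1% | 77.6% | 9.5 |
| 0.7 | 106 | 80.1% | 86.1% | 5.9 |
| 0.8 | 106 | 93.0% | 95.2% | 2.2 |
| 0.7 | 152 (no dropout) | 92.0% | 95.5% | 3.4 |

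Gains are taken before rounding.

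**Step 5: diabetes.** The protocol gives no figure for the association of diabetes with MCS, so no gain can be derived. Purely as an assumption, if diabetes explained 1% to 5% of the residual variance, adding it to the ANCOVA would bring roughly 0.3 to 2 further points at 106 per arm.

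**The case against.** The strongest reply is that nothing here is wrong. The planned test holds its 5% level, is unbiased under randomisation, matches the sample size calculation and delivers the 80% power it was sized for. All of that stands. The gain is also modest in absolute terms: about 0.16 AU of half-width against a 3-AU threshold, and less if the correlation is high or dropout is low.

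A reader might infer three stronger points that the protocol does not support.
- **That the analysis ignores baseline.** It does not. The change score uses baseline, with the slope fixed at 1. An analysis without baseline would need about 175 per arm, not 106.
- **That the diabetes stratum is wrongly left out and accounts for part of the lost power.** Section 10.3 is silent on covariates and excludes none. A covariate list is commonly left to a SAP, which is not at hand. The whole gain of about 6 points comes from baseline adjustment.
- **That the change score is biased by chance imbalance.** A one-SE baseline difference (10 × √(2/106) = 1.37 AU) would shift the estimate by 0.3 × 1.37 = 0.41 AU in that sample. Such shifts average to zero over randomisations, so this is the efficiency point in another form.

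Leaving the matter to a SAP does not fully answer it. The protocol does not leave the primary method open; it names one, and a different one should be settled there.

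**Conclusion.** This is a free improvement to a valid and internally consistent plan. On the protocol's own inputs, ANCOVA raises power at 106 per arm from 80.1% to 86.1%, cuts variance by 15% and narrows the 95% CI half-width from 2.10 to 1.93 AU. Put the other way, it would reach 80% with 90 per arm instead of 106.

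The size rests on equal SDs at the two visits, on the assumed correlation and on how many participants are retained. Over the cases tabulated it runs from about 2 to 9.5 points. The practical value is greatest if the correlation is below 0.7: at 0.6 the planned test falls to 68%, while ANCOVA stays near 78%. The trial is not underpowered by the present choice on its own assumptions, and no part of the gain can be credited to diabetes.

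**What to change.** - **Section 10.3:** name as the primary analysis an ANCOVA of week-12 MCS on randomised arm and baseline MCS. Report the adjusted mean difference with its 95% CI against the 3-AU threshold. Use the same form for the other continuous outcomes, each with its own baseline value.
- **Section 10.3:** include the diabetes randomisation stratum as a covariate, so that the analysis reflects the allocation scheme. It costs nothing, but its gain cannot be quantified from the protocol.
- **Section 10.1:** keep N = 304, and note that 106 per arm gives about 86% power under ANCOVA at a correlation of 0.7.

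The cost is wording only. Baseline MCS and diabetes status are already collected, and no visit, participant or measurement is added. Because a named primary method changes, the amendment should be made before any data are seen by arm.

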### 6.4 Randomisation Procedure

Randomisation (1:1) will be done on a secure web-based service. After passing the screening visit and when all eligibility criteria have been confirmed and informed consent has been received, the participants can be randomised into the study. Participants will be randomised using an approach based on randomly varying block sizes.

Randomisation will be done only by an unblinded member of staff who has been delegated this responsibility by the principal investigator as evidenced by documentation in the delegation log. The web-based database will allocate the participant a unique trial identification number and their identification details will be entered onto the trial identification log, which is kept in the Investigator Site File.

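### The primary MCS analysis may switch, on the trial's own data, to a non-parametric test that the protocol does not identify and that does not estimate the mean difference behind the sample size

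*Protocol*

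**What the plan says.** Section 4.1.1 of the protocol defines the primary outcome as "Mental HRQoL as measured by MCS of the KDQOL-36 at 12 weeks". Section 10.3 analyses it by repeated measures ANOVA, comparing change over 12 weeks between the arms, and groups it with the other outcomes expected to be parametric. The next sentence reads: "If the assumptions for parametric testing are not met, the equivalent non-parametric equivalent tests will be performed". MCS is not excluded from it, and it does not say which test, or which estimate, would then carry the result. Section 10.3 also states: "Statistical significance will be set at 5% and tests will be two-sided".

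Section 10.1 sizes the trial "based on an MCS with a mean of 45, SD 10 and correlation between repeated measures of 0.7", which with 106 per group "would allow a clinically meaningful difference of 3AUs to be detected at 80% power and 5% alpha". Those inputs describe means on the MCS scale.

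**The concern.** The choice of primary analysis is made to depend on the outcome data, and the replacement is described only as an equivalent. The planned model has two factors, arm and time, and more than one rank method could be offered in its place. Section 10.3 speaks of change, which points to Mann-Whitney on change scores. Section 4.1.1 defines the outcome as the score at 12 weeks, which leaves room for Mann-Whitney on week-12 scores. Aligned-rank methods are a third option. These tests differ in power and can disagree on significance.

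Two things are at stake. If the test is settled only after the data are seen, the 5% level is no longer assured. And if the switch is made, the main result need not be the difference in mean MCS on which the trial was sized, so its comparison with 3 AU changes meaning or may not be reported at all.

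**Working it through.** **Inputs.** Difference 3 AU, SD 10, correlation 0.7, 80% power (Section 10.1); 5% two-sided (Section 10.3); 1:1 allocation (Section 6.4).

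**1. The plan's own figure.** SD of change = 10 × √(2 × (1 − 0.7)) = 7.746. By the normal approximation, n per group = 2 × (1.960 + 0.8416)² × 7.746² / 3² = 2 × 7.849 × 60 / 9 = 104.7, so 105. With the t distribution it is 105.6, so 106, as stated. Dropout: 106 / 0.70 = 151.4, so 152 per arm and 304 in all, as stated. Other sizings do not match: ANCOVA, with SD 10 × √(1 − 0.49) = 7.141, needs 89 per group; week-12 scores alone, with SD 10, need 175. The sample size therefore rests on a difference in mean change.

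**2. Power at 106 per arm for 3 AU, normal data.** Power = Φ(3 / (SD × √(2/n)) − 1.960). For rank tests, n is multiplied by 3/π, giving 106 × 3/π = 101.2.

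- Mean change, SD 7.746: 80.5% (80.1% with the t distribution)
- ANCOVA, SD 7.141: 3 / (7.141 × √(2/106)) = 3.058, so Φ(1.098) = 86.4%
- Mann-Whitney on change: 78.7%
- Mann-Whitney on week-12 scores, SD 10: 56.9%
- t-test on week-12 scores, SD 10: 3 / (10 × √(2/106)) = 2.184, so Φ(0.224) = 58.9%

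The last two lines show that the large drop comes from discarding baseline, not from using ranks.

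**3. Simulation of the switch.** 4,000 trials per scenario, 106 per arm. Two features are assumptions, because the protocol gives neither: a Shapiro-Wilk trigger at 5% on the change scores of either arm, and a moderate left skew (gamma, shape 4).

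| | Normal | Moderate left skew |
| --- | --- | --- |
| Trigger fires | about 10% | about 53% |
| Type I error, t-test on change | 5.4% | 5.2% |
| Type I error, switch fixed in advance to Mann-Whitney on change | 5.7% | 5.1% |
| Type I error, switch fixed in advance to Mann-Whitney on week 12 | 5.5% | 5.5% |
| Type I error, best of the three tests | 11.1% | 10.9% |
| Power, t-test on change | 80.1% | 79.0% |
| Power, Mann-Whitney on change | 77.7% | 82.7% |
| Power, Mann-Whitney on week 12 | 56.9% | 66.0% |
| t on change and Mann-Whitney on change disagree (true 3 AU) | 5.3% | 6.1% |
| t on change and Mann-Whitney on week 12 disagree (true 3 AU) | 37.4% | 32.3% |

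The simulation error of a rate near 5% is √(0.05 × 0.95 / 4000) = 0.34 percentage points.

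**4. Strong skew (assumed: lognormal type, sigma 0.5, skewness about −1.75).** Type I error is 5.0% for the t-test on change and 5.2% for ANCOVA. Power for 3 AU is about 78% for the t-test on change, 84% for ANCOVA and 88% for Mann-Whitney on change.

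**5. Estimates.** In 3,000 simulated trials per scenario with a true shift of 3, the Hodges-Lehmann estimate on change averaged 3.00 with normal data and 3.03 under strong skew. The mean difference averaged 3.00 and 3.02. The two agree here because the simulated effect is a pure shift; they need not agree if the intervention also changes the shape of the distribution.

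**The case against.** The strongest defence is that the wording is less open than it looks. With two arms and two visits, the planned group-by-time test is the two-sample comparison of mean change. Its natural rank counterpart is Mann-Whitney on change, which compares the randomised arms, uses baseline and can report a shift in MCS units. Naming the test and the check is commonly left to an SAP, which may exist, and Section 15 gives the analysis to an independent statistician. Much of this stands, and it rules out several stronger readings that a reader might infer:

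- *That no rank test could compare the arms, or that every MCS-scale estimate is lost.* Mann-Whitney on change with a Hodges-Lehmann interval does both. The protocol simply does not commit to it.
- *That the rule raises type I error to 11%.* That figure needs free choice among three tests, which the protocol does not grant. A switch to one test fixed in advance stays near 5%.
- *That going to ranks cuts power to 57%.* That follows from dropping baseline, which the protocol does not propose. Mann-Whitney on change loses only about 2 points with normal data.
- *That the switch has no benefit.* Under strong skew the rank test on change beats the planned test by about 10 points (88% against 78%).
- *That MCS will be skewed.* Nothing in the protocol says so; the skewed shapes are assumptions.

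The defence does not remove the core point. The missing name could be supplied in an SAP, but the protocol itself commits the primary outcome to a data-driven change of test and does not tie the result to the quantity used for sizing. It is also fair to say that moving to ANCOVA goes beyond repairing the fallback sentence. Exempting MCS would settle the switch on its own; ANCOVA is recommended because the same inputs show a clear gain.

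**Conclusion.** The concern holds in a limited form. For the primary outcome, Section 10.3 leaves open which test replaces the planned one and what effect it estimates, whereas the 106 per group in Section 10.1 reproduces only as a comparison of mean change. The exposure lies between a type I error of about 5%, if one replacement is fixed before the data are seen, and about 11%, if three tests remain open. With normal data and a true 3 AU effect, the choice of replacement moves power between about 78% and 57%.

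The switch is not needed to protect the error rate. At 106 per arm, mean-based tests stay at about 5% under both skewed shapes tried. These results rest on the plan's SD and correlation, on 106 analysed per arm, and on the assumed trigger and shapes. This is a weakness worth correcting before analysis. It does not invalidate the design, and the sample size needs no change.

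**What to change.** In Section 10.3, and in the SAP to match:

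- Exempt MCS from the non-parametric fallback.
- Make the baseline-adjusted difference in mean MCS at 12 weeks (ANCOVA), with its 95% CI, the primary result whatever the distribution.
- Name one sensitivity analysis in advance: a bootstrap or robust-standard-error interval for the mean difference, or Mann-Whitney on change scores with a Hodges-Lehmann estimate and CI.
- Keep a rank fallback, if wanted, for skewed secondary outcomes such as GPAQ minutes.

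The cost is a wording change; 304 recruits still suffice. With normal data, power for 3 AU rises from about 80% to 86%. The price is paid only under strong skew, where ANCOVA would have about 84% power against 88% for the rank test on change, though still more than the 78% of the planned test on change.
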